## Abstract

**Background:**

Postnatal depression (PND) is the most common disorder of the puerperium with serious consequences for both mother and child if left untreated. While there are effective treatments, there are many barriers for new mothers needing to access them. Prevention strategies may offer a more acceptable means of addressing the problem. Internet interventions can help overcome some barriers to reducing the impact of PND. However, to date there are no published studies that investigate the efficacy of internet interventions for the prevention of PND.

**Methods/Design:**

The proposed study is a two-arm double blind randomised controlled trial. 175 participants will be recruited in the immediate postnatal period at an Australian community hospital. Women who meet inclusion criteria (internet access, email address, telephone number, over 18, live birth, fluent English) will complete the Edinburgh Postnatal Depression Scale (EPDS). Those with a score above 9 will undertake the Structured Clinical Interview for DSM Disorders (SCID). Those with a clinical diagnosis of depression, or a lifetime diagnosis of bipolar disorder or psychosis on the SCID will be excluded. Following completion of the baseline battery women will be randomised using a computer-generated algorithm to either the intervention or control condition. The intervention will consist of 5 modules of automated, interactive cognitive behaviour training (CB training), completed weekly with email reminders. The control will replicate the level of contact participants experience with the intervention, but the content will be of a general health nature. Participants will complete questionnaires immediately post-intervention (6 weeks) and 3-, 6- and 12 months follow-up. There will also be a second SCID delivered via telephone at 6 months. We hypothesise that relative to the control group, the intervention group will show a greater reduction in postnatal distress on the EPDS (primary outcome measure). We also hypothesise that the intervention group will demonstrate lower levels of anxiety and stress and higher levels of parenting confidence than the control group following intervention and/or follow-up.

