### Sample size

Based on power calculations, an estimated minimum of 112 participants are required. Assuming a correlation of .5 between baseline and endpoint outcome measures, a 20% dropout, and an effect size of 0.43 [10], this sample size will have the power at 80% to detect differences at endpoint of .54 standard deviations (alpha = 0.05, non-directional test). Approximately 3000 babies are born per year at The Canberra Hospital. 20% of their mothers will score over 9 on the EPDS immediately after birth [33,41], yielding a potential pool of 600 women per year. Of these women, roughly 4% [42] will be clinically depressed and therefore excluded, leaving a potential pool of 576. Based on rates of recruitment from community samples, we anticipate that 25% of these potential participants will agree to participate in the study, yielding a sample of 144 women per year. Allowing for a further 10-20% unexpected drop-out after recruitment and before randomisation this should be sufficient to reach the target sample size of 112 participants.

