### Randomisation

Participants will be randomised to one of the two website conditions using a computer-generated algorithm that is replicable and validated. The start value for the seed will be determined from the current server time and will be recorded for replication. Randomisation will not be stratified and will occur automatically at the completion of the baseline survey by taking the next allocation of the generated schedule.

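### The abstract plans to recruit 175 and the sample-size section targets 112, with no link between them; 112 is worded as a number randomised but reproduces only as a number analysed

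*Protocol article*

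**What the plan says.** The abstract of the protocol article, under Methods/Design, states: "175 participants will be recruited in the immediate postnatal period at an Australian community hospital".

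The Sample size section starts from a different number: "Based on power calculations, an estimated minimum of 112 participants are required". Its inputs follow: "Assuming a correlation of .5 between baseline and endpoint outcome measures, a 20% dropout, and an effect size of 0.43". The section says that this size gives 80% power for a difference of 0.54 SD at endpoint, two-sided alpha 0.05.

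A recruitment estimate comes next. Births, the share scoring above the EPDS cut-off, the exclusion of clinically depressed women and a 25% agreement rate are multiplied, "yielding a sample of 144 women per year". The section then deducts another 10-20% lost between recruitment and randomisation, and concludes that "this should be sufficient to reach the target sample size of 112 participants".

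The figure 175 does not occur in the Sample size section, and 112 does not occur in the abstract. The article gives no recruitment period.

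**The concern.** A trial needs three linked counts: women recruited, women randomised and women analysed. This article gives two numbers and does not say which count either refers to.

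The Sample size section can be read in two ways. Its wording points to 112 randomised: the 20% dropout is among the assumptions behind 112, the loss before randomisation is presented as additional, and the yearly yield after that loss is compared directly with 112. Its arithmetic points to 112 analysed, because the calculation returns 112 only when no dropout allowance is made.

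The size of the trial depends on the answer. Closing at 112 randomised instead of 140 removes a fifth of the analysed sample (90 against 112). A reader of the results could also not tell whether a trial that stopped at 112, 140 or 175 had met its plan.

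**Working it through.** **Inputs.** From the Sample size section: N = 112, r = 0.5 between baseline and endpoint, dropout 20%, cited effect size 0.43, detectable difference 0.54 SD, power 80%, two-sided alpha 0.05, 144 recruits a year, pre-randomisation loss 10-20%. From the abstract: 175. The Randomisation section names two conditions but no ratio, so 1:1 is assumed.

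**1. Reproducing 112.** The normal approximation is n per arm = 2 × [(1.96 + 0.8416)/d]².
- At d = 0.54: 2 × (2.8016/0.54)² = 53.8, so 54 per arm, 108 in total. The t-test needs 54.8, so 55 per arm, **110 in total**. With 112 analysed, t-test power is 81%.
- At d = 0.43/0.8 = 0.5375 the t-test needs exactly 112. This may be how 0.54 arose, but the article does not say so.
- A change score at r = 0.5 has variance factor 2(1 − 0.5) = 1, so it needs the same N as the unadjusted comparison.

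None of these includes dropout. The variants that do, or that use r in an ANCOVA, miss 112:

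| Basis, at 0.54 SD | Analysed | Randomised with 20% dropout |
|---|---|---|
| t-test, unadjusted | 110 | 110/0.8 = 137.5 |
| 112 taken as analysed | 112 | 112/0.8 = 140 |
| ANCOVA, variance factor 1 − r² = 0.75 | 82 | 82/0.8 = 102.5 |

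So 112 is reproduced as an analysed number, and the stated 20% dropout cannot be found in it.

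**2. Power if 112 is the number randomised.** Analysed: 112 × 0.8 = 89.6, about 90. The adjusted columns divide d by √0.75 (r = 0.5). All power figures are from the t-test; the normal approximation gives about one point more or less.

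| Randomised | Analysed | 0.54 SD, unadjusted | 0.54 SD, adjusted | 0.43 SD, unadjusted | 0.43 SD, adjusted |
|---|---|---|---|---|---|
| 112 | 90 | 72% | 83% | 52% | 64% |
| 140 | 112 | 81% | 90% | 62% | 74% |
| 175 | 140 | 89% | 96% | 71% | 83% |

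**3. Where 175 could come from.**
- Two successive 20% losses: 112/0.8 = 140 and 140/0.8 = 175 exactly. This takes the upper end of the 10-20% range; the lower end gives 140/0.9 = 156.
- An unadjusted t-test at the cited 0.43 SD needs 86 per arm, 172 in total. At 175 its power is 81%.

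**4. The recruitment estimate.**
- 3000 × 0.20 = 600; × 0.96 = 576; × 0.25 = 144 a year. The section's own figures reproduce.
- Less 10-20%: 144 × 0.9 = 129.6 and 144 × 0.8 = 115.2, so 115 to 130 randomised a year.
- Less 20% dropout: 129.6 × 0.8 = 103.7 and 115.2 × 0.8 = 92.2, so 92 to 104 completers a year.
- If 112 means randomised, 112/0.9 = 124 to 112/0.8 = 140 recruits are needed, and one year's 144 is enough.
- If 112 means completers, 156 to 175 recruits are needed. At 144 a year that is 156/144 × 12 = 13.0 to 175/144 × 12 = 14.6 months.

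**The case against.** The strongest reply is that nothing here conflicts. The section calls 112 a minimum, and planning to recruit 175 is compatible with a minimum of 112. This stands. A reader might infer that the two figures can be reconciled only if 112 means completers, but the documents do not support that: the 175-140-112 chain is exact arithmetic but is written nowhere, it needs the upper end of the pre-randomisation loss, and 172 at 0.43 SD is a rival source.

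A reader might also infer that the sentence on sufficient recruitment is false. That is not shown. Under the section's own wording, 115 to 130 randomised a year meets 112. Under the completer reading a single year falls short, but the article sets no time limit, and 112 completers would follow in 13 to 15 months.

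Third, it can be said that power is adequate even on the smallest reading. With baseline adjustment at the stated correlation, 90 analysed women give 83% power at 0.54 SD. This also stands, so the plan cannot simply be called underpowered at the difference it names. It does not rescue 112, however: an adjusted calculation with 20% dropout gives about 103, so 112 was not reached that way either. The lower powers at 0.43 SD reflect the separate question of which effect size the trial is built on.

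What the reply leaves untouched is that 175 is unexplained, and that the wording and the arithmetic behind 112 disagree on what is being counted.

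**Conclusion.** The point holds as an inconsistency in how the sample size is stated. The abstract and the Sample size section give 175 and 112 without a link. The section words 112 as randomised with dropout included, but 112 matches its stated power only as the number analysed. Under the unadjusted calculation that reproduces 112, the randomised number should be about 137 to 140. Randomising 112 instead leaves about 90 analysed and reduces power at 0.54 SD from about 81% to 72% unadjusted, or from 90% to 83% if the analysis adjusts for baseline.

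This rests on 1:1 allocation, on a comparison of two means at one endpoint, and on 20% dropout meaning women without endpoint data. A mixed model that uses partial follow-up may recover some of that loss. The origin of 175 remains open.

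**What to change.** State one chain in the abstract and in the Sample size section: number recruited, number randomised, number analysed, with the loss assumed at each step. If the authors' chain is 175 recruited, 140 randomised and 112 analysed, a single sentence says so; if 175 came from another calculation, show it.

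Name the number randomised as the recruitment target. Attach the 80% power statement to the number analysed, and say which analysis it assumes (unadjusted, change score or baseline-adjusted), so that the role of r = 0.5 and of the 20% dropout can be seen.

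If 112 means completers, reword the recruitment sentence to say that more than one year is needed, about 13 to 15 months at 144 recruits a year. If 112 means randomised, that sentence can stay, but the power statement must then refer to about 90 analysed.

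The cost is a few sentences in two places. Choosing 140 randomised over 112 also means 28 more women to randomise.

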**Discussion:**

The proposed study addresses a number of limitations of earlier trials.

**Trial registration:**

Australia and New Zealand Clinical Trials Registers, ACTRN12609001032246.

## Background

Postnatal depression (PND) is defined by the Diagnostic and Statistical Manual of Mental Disorders (DSM-IV) [1] as an episode of major depression commencing within the first 4 weeks postpartum. In practice, most researchers and clinicians broaden the onset period to include any time in the first 12 months postpartum. With a prevalence rate of approximately 13% [2], PND is the most common complication of the puerperium. Not only is PND relatively common, but it also has a profound effect on both mother and child. Women experience low mood, low satisfaction with parenting and feelings of guilt. In extreme cases they may attempt or complete suicide or infanticide. Studies of infants have shown that the effects of PND on the child, including poor attachment and cognitive deficits, persist well into childhood [3].

As with other depressive disorders, there are a number of effective treatments for PND including antidepressant medication and psychotherapy. However there are unique barriers to implementing treatments for PND. The first is that breastfeeding women may be unwilling to take antidepressant medications for fear of the effects on their baby [4,5]. Secondly, new mothers are often time-poor and this can be a major barrier to undertaking cognitive behaviour therapy (CBT) [6]. Women with a new baby are typically unable to schedule lengthy sessions with a health professional. Finally, new mothers may be particularly susceptible to perceived and self-stigma. Stigma may serve as a barrier to help seeking for any type of depression. However, new mothers with depression may be subject to the additional concern that they will be perceived as a “bad mother” as a result of their condition. As a consequence they may refuse to seek help, refuse treatment when diagnosed, and even refuse to accept a diagnosis of depression [7]. Because of these unique barriers, prevention of PND, rather than treatment, may be a particularly appropriate course to pursue.

There has been substantial research into the prevention of PND. A recent review [8,9] found that prevention programs delivered postnatally only were more beneficial than those that included an antenatal component. Also, interventions delivered individually were more effective than those delivered to groups. Some prevention studies have focussed on models of care, where the delivery of service has been the focus, rather than the content of the intervention. Some of these models include postnatal layperson follow-up and home-based care. These strategies have not been particularly effective [8,9]. This is not surprising, given that the content of many of these interventions (support and/ or education about PND) was not necessarily selected on the basis of demonstrated efficacy in other contexts. Other studies that have used individual or group therapy based on Cognitive Behaviour Therapy (CBT) or Interpersonal Therapy (IPT), which are of known efficacy in *treating* postnatal depression, have been more successful in reducing symptoms and preventing the development of PND [10-14]. This type of intervention however, is expensive. Prevention involves delivering interventions to large numbers of women. To provide individual or group therapy to such numbers is costly and unlikely to constitute a feasible strategy for preventing PND.

### Rationale for the proposed study

The Internet offers a potential means for addressing the barriers associated with the delivery of conventional prevention programs to women in the post natal period. Such programs can be accessed online without cost. They do not require time consuming, and inconveniently scheduled, trips to face-to-face sessions. Rather, a mother can access the intervention at times and for periods which are short enough to fit into their baby’s variable and demanding schedule. They can do as much or as little at a time that suits them. Moreover, the anonymity of accessing an Internet intervention may overcome the stigma associated with seeking help for the subclinical symptoms of PND [15]. It may be argued that there are inequities inherent in an Internet-delivered intervention; however, this inequity of access is no greater, and arguably less than with traditional interventions. In many jurisdictions, those disadvantaged women who do not have access to the Internet are also unlikely to be able to afford face-to-face interventions. Additionally, within the geographical area of this trial, around 90-95% of the target population has Internet access [16].

There is now convincing evidence that Internet-based programs based on CBT are effective for treating depression [17]. There is also evidence of their efficacy in preventing depression [18-20]. To date there have been no published studies of the efficacy of internet interventions for treating or preventing PND. However, we have undertaken a pilot survey of young mothers (n = 34, unpublished) to examine the acceptability of an automated CB Training web-based program for PND. The findings suggest that such a program would be acceptable to this group.

Therefore, the current study seeks to evaluate the efficacy for preventing PND of an Internet intervention program, MoodGYM. This automated Cognitive Behaviour Training (CB Training) web-based program has been demonstrated in randomised controlled trials to reduce depressive symptoms in members of the community at risk of depressive disorder [20] and to prevent new cases of depression and anxiety in young people [19]. Since a recent meta-analysis concluded that the most effective preventions have been delivered solely in the postnatal period [8,9], the proposed intervention will be undertaken in this period.

Previous studies of the efficacy or effectiveness of PND prevention programs have been characterised by a number of weaknesses. One key limitation is that they have failed to employ an adequate control condition often using instead a usual care scenario e.g. [21-23], or wait list control e.g. [24] neither of which explicitly controls for the effects of the increased contact with staff. The current study will employ an attention control condition that matches the level of contact provided to the intervention group. Another limitation of previous PND prevention studies is that they have failed to exclude women with a current diagnosis of PND. Our proposed study will exclude women with an existing disorder enabling the true prevention effect of the intervention to be examined in the absence of confounding from treatment effects.

## Methods/Design

### Design

A 2 (Condition) X 4 (Time) double blind, randomised controlled design is planned. Participants will be randomly allocated to either the online intervention or an online control condition. Outcomes will be assessed at baseline, post-intervention (6 weeks), 3 months, 6 months, and 12 months post-randomisation.

### Participants

Participants will be recruited in the maternity (postnatal) ward and birthing centre of The Canberra Hospital in Canberra, Australia. Women will be eligible for the trial if they have internet access, an email address, a telephone number, are over 18, have had a live birth, can read and write English, and score over 9 on the Edinburgh Postnatal Depression Scale. Women who are currently receiving formal psychological treatment will be excluded from the trial. Potential participants will be asked if they are seeing a health professional for a mental health condition and if so, the nature of their treatment. If the treatment they are receiving is any of the ‘talking’ therapies, they will be excluded. Those receiving exclusively pharmacological interventions will be not be excluded. Women with a current diagnosis of a depressive disorder, or a history of mania or psychosis will also be excluded (based on SCID modules A and B – Mood Episodes and Psychotic Symptoms). Women who endorse self-harm items will also be excluded.

### Measures

The primary outcome will be postnatal distress. The secondary outcomes will be the severity of depressive and anxiety symptomatology, parenting confidence and diagnostic status. These will be measured as follows:

1. *Postnatal distress* will be measured online using the Edinburgh Postnatal Depression Scale (EPDS) [25]. The most widely-used measure of postnatal depression and anxiety, this instrument contains 10 items and takes around 5 minutes to complete. Answers are scored between 0 and 3, and summed for a total score (range 0 to 30) with higher scores indicating higher levels of postnatal distress. The validity of the EPDS has been established within the Australian population [26], for online administration [27] and for use in the immediate postpartum period to predict PND outcomes e.g. [28,29]. The cut-off used in this study (over 9) is that recommended by Matthey *et al.*[30] for probable minor depression.

Secondary outcomes

2. *Depressive and anxiety symptomatology* will be measured online using the Depression, Anxiety and Stress Scale (DASS) [31], a 21 item self-report questionnaire designed to measure the severity of symptoms. This self-report measure has adequate psychometric characteristics [32] and has been previously used in this population [33].

3. *Parenting confidence* will be assessed using the 15-item self-report Karitane Parenting Confidence Scale (KPCS) [34]. Although the KPCS is a new measure, it shows good test-retest reliability and internal consistency. The scale was developed and tested in Australia, making this a particularly appropriate instrument for the current study. The KPCS will be delivered via the Internet.

4. *Depression Status* will be evaluated using the Structured Clinical Interview for DSM Disorders (SCID) Module A (Mood Episodes). The SCID is a structured interview for current and past diagnoses of DSM-IV disorders. There have been a number of reliability studies yielding an acceptable range of Kappa values for the diagnosis of major depression (from 0.61 [35] to 0.93 [36]). At baseline this interview will be delivered face-to-face; however, at 6-months follow-up it will completed via telephone [37].

5. *Risk factors* to be assessed by self-report include: health of infant, sex of infant, infant feeding status and satisfaction, infant feeding and sleep patterns, major life events, and difficulty of pregnancy and delivery. Each of these will be assessed with a single item. For example, “How satisfied are you with your birth experience with this baby” has a 5-point Likert Scale from ‘Very satisfied’ to ‘Very dissatisfied’. We will also assess level of maternal support using the Maternal Social Support Scale, and personal history of depression through the SCID. All risk factor items will be administered as part of an online battery, with the exception of the SCID.

6. Cognitive behaviour therapy literacy and stigma will be assessed using an online delivery of the CBT literacy scale and the Depression Stigma Scale (DSS) [38,39]. The CBT literacy scale has previously been successfully used to assess change in CBT knowledge following a MoodGYM intervention [20] and the DSS has adequate reliability and validity.

7. *Socioeconomic factors* will be assessed online, including self-reported age, marital status, education level, occupation, income, and parity.

### Conditions

#### The intervention condition: MoodGYM

MoodGYM is an online, interactive program delivering cognitive behaviour training. The program consists of five modules which take between 20 and 40 minutes to complete. However, participants will be able to choose to spend as much or as little time as they wish in a given session. Module 1 (Feelings) will help participants to identify negative thinking patterns. Module 2 (Thoughts) will assist them to identify inaccurate and biased ways of thinking. Module 3 (Unwarping) will present methods for changing their negative and biased habitual thinking patterns. Module 4 (De-stressing) will focus on stress management and relaxation techniques. Finally, in module 5 (Relationships and Problem Solving), the participant will be provided with techniques for coping with difficult relationships. It will also introduce the concept of simple problem solving. Each module includes some work that is completed immediately and some that users return to and expand (the users’ ‘Workbook’). Some examples of these ‘Workbook’ exercises are identifying unhelpful thought patterns and using specific tools to contest them. Users can also schedule pleasant activities, and other ‘homework’ exercises.

Participants will complete one module per week. They will be required to complete each module before they can proceed to the next. Participants will be sent an automated email each week to inform them when the next module is available. Participants can complete each module at their own pace. However, a reminder will be sent if the participant fails to log in to the website within four days of receiving the initial notification that the next module is available.

